## Methods

### Survey Description

In late 2018, as part of an impact evaluation of the maternal messaging program Kilkari, a randomly selected sample of 5095 women 4-7 months pregnant, with access to a mobile phone were identified across four districts of Madhya Pradesh, India: Rewa, Rajgarh, Hoshangabad, and Mandsaur [6]. Identified women were administered a structured baseline survey tool that sought to measure their knowledge of reproductive, maternal, newborn, and child health (RMNCH) practices and observe their digital literacy. Following the baseline survey, women were randomized to receive Kilkari messages or not (status quo). In this paper, we focus on the QA procedures for the endline survey administered to women enrolled in the study at 12 months postpartum. The endline survey will be used to capture RMNCH decision making, discussion, knowledge, and practice.

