#### Enumerator Recruitment and Training

Enumerator recruitment depends on survey size and timeline, as well as the characteristics of the enumerator. The experience and characteristics, including age, gender, caste, ethnicity, education, and geographic origins of an enumerator can influence not only their understanding of survey questions but also the implementation of the survey, including how they explain questions to and interact with respondents. Survey enumerators will be women fluent in Hindi, between 21-35 years of age, with education levels ranging from current college students to current PhD students, and 0-12 years of survey experience. To monitor the effects of enumerator characteristics and experience on data quality, we will start by administering a short survey during training to formulate their profile, and then as survey data are collected, use these profile data to understand potential associations between profile data and survey data quality.

To ensure that adequate numbers of enumerators are recruited, we have projected the number of interviews that need to be completed weekly by geographic area and considered the time it takes to administer each survey coupled with the time required to travel to and locate respondents. Additional factors such as enumerator attrition, along with the need to conduct repeat visits to locate respondents or complete partially completed surveys, will be factored in.

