#### Field Coordination

Beyond the development of the tool and enumerator selection and training, the quality of data is improved by strong field coordination. Field coordination is built on two main components: field and logistics planning as well as coordinating the monitoring of data collection through supervisors and checks. First, key eligibility criteria for interviews need to be kept in mind when planning field logistics. Women will be interviewed if they have completed 12 months postpartum or longer; thus, field planning will require that enumerators be spread across four districts of Madhya Pradesh to capture women as they reach their expected date of eligibility. Confirming women’s eligibility will require reliability monitoring, as outlined below. Once an eligible woman is identified, supervisors are given her identification and location information so they can coordinate their team of enumerators to her location and manage any follow-up visits as necessary depending on her availability.

A clear hierarchy in quality assurance activities as part of field operations is key for ensuring the collection of high-quality data. The field team will include 35 enumerators, 9 supervisors, and 2 coordinators, a survey coordinator, and a field manager. The male supervisors will be paired with a team of enumerators, consisting of 3-4 female enumerators, and will be in charge of checking the data as it is collected. The coordinators track adverse events and logistics and will conduct spot checks. The survey coordinator will monitor the data and relay any issues back to the larger research team. The field manager will handle training as well as ensure the field plan is in place. With clear roles in place, the field manager and survey coordinator will be best able to plan the fieldwork and monitoring, respectively. The data flow and feedback processes are outlined below (Figure 2).

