##### 3. Building Models

This data will be split randomly into a training set and a testing set. As predictors of the models, we will use the features listed in step 1, and the data will be labeled as “false” or “true.”

Two steps will be undertaken to build models: (1) develop the best models for each learning algorithm using the training dataset and cross-validation methods and (2) apply the best performing algorithm on the test dataset for an unbiased evaluation. During the learning (training) process, k-fold cross-validation methods will be used to avoid overfitting and assess model performance. The k-fold cross-validation method involves splitting the dataset into k-subsets, which are, in turn, held out while the model is trained on all other subsets. The process is complete when accuracy has been determined for each instance in the data set, and an overall estimate of accuracy has been generated. Once the learning step is accomplished on the “training” set, we have trained models. Each model will be tested using the originally withheld testing set.

The algorithms under consideration are listed below in Table 2. We aim to train using all methods to identify the best algorithm for our data. Methods to assess the models, compare their attributes, and formulas to compare the results of the learning algorithms are similar to those presented in a study by Mohan et al [3]. That study also describes comparisons of the strengths of these various algorithms [3].

**Table 1 table1:** Biases in survey completion that can be captured using machine learning.

Biases	Indicator	Numerator	Denominator
Rushed completion	Percent of time to complete survey, sections, and individual question as compared to time recorded during piloting	Time measured during the pilot—actual time in seconds	Pilot time
CAPI^a^ entry error/ Fabricated responses	Percent difference from 10% resample	Questions that are different in 10% resample	Total number of questions resampled
Respondent bias	Mean time taken to complete questions among respondents in differing sociodemographic characteristics	N/A^b^	N/A
Skipping of sections	Percent of skips across all potential skip options throughout the tool	Opportunities where a skip was implemented	Total opportunities where a question or section can be skipped

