The limitations of this approach include the parameters used for the machine learning approach—ideally more time-stamps and information on tapping forward or back off a screen would provide more detail on the timing and mechanics of each survey completed. In some cases, an interview may be interrupted by factors outside the enumerator’s and respondent’s control such as a baby crying or a neighbor calling; however, the enumerators are encouraged to do their best to complete the survey in one sitting and include comments on hindering circumstances that extend the length of the interview at the end of the survey. Additionally, some skips in the surveys and “don’t know” responses are necessary and unavoidable; thus, these measures could be ambiguous at times. Given the nature of our multi-select tool, we expected enumerators to be probing for answers and using “other specify” for ambiguous answers and using the “don’t know” option minimally. However, this parameter is specific to our survey, and it could be that in another type of tool, other parameters are used to indicate rushed or low-quality interviews. This difference is true of other steps as well, such as which time-stamps to collect, what kind of labeled data to obtain, and the types of responses that are useful for quality control. Quality assurance needs to be tailored for each survey.

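### As defined in Table 1, the 'respondent bias' indicator does not separate respondent effects from enumerator or district pace

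*Protocol article*

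**What the plan says.** The protocol article, under step 1 of Data Analytics (selecting features), points to Table 1 for the indicator proposed for each feature. Table 1, printed under step 3 (3. Building Models), gives for respondent bias: "Mean time taken to complete questions among respondents in differing sociodemographic characteristics". Numerator and denominator are marked not applicable. No reference group, enumerator term, district term or treatment of interrupted interviews is given.

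Other sections bear on how that mean can be read:

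- Enumerator Recruitment and Training says that the experience and characteristics of an enumerator "can influence not only their understanding of survey questions but also the implementation of the survey". It plans a short profile survey so that these effects can be studied.
- Field Coordination says that "field planning will require that enumerators be spread across four districts of Madhya Pradesh". Supervisors receive each woman's location "so they can coordinate their team of enumerators to her location". It also states: "The field team will include 35 enumerators, 9 supervisors, and 2 coordinators".
- Step 1 links the survey data to the enumerator profiles. Table 2 lists times among the quantities to be classified or grouped by enumerator and respondent characteristics.
- The Discussion accepts that "an interview may be interrupted by factors outside the enumerator’s and respondent’s control", and asks enumerators to note such circumstances in comments at the end of the survey. No section says how those comments will be used.

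**The concern.** The label names a cause, the respondent, but the stated measure is a group mean of elapsed time. Interviews reach enumerators through geography and date of eligibility, not by random allocation. If one team or district is slower, and a sociodemographic group is more common there, that group's mean time rises even though its members answer no differently from anyone else.

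Table 1 also uses time for a second bias, rushed completion, which is enumerator behaviour. A group mean of time cannot tell the two apart.

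What is at stake is where corrective effort goes. The section on feedback loops allows that a set of the respondent population may need to be dealt with differently if a problem is pervasive. Team pace misread as a respondent effect could direct attention to a caste or education group and away from the team that needs it.

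**Working it through.** The plan gives no figure for this indicator (no variance, threshold or power), so there is nothing to reproduce. The check is an illustration of how large the artefact could be.

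**Inputs from the article**
- Sample: 5095 women (Survey Description).
- Scheduled tribe: 11% of the sample (Study Setting and Population), so 0.11 × 5095 ≈ 560 women, leaving 4535 others.
- Mean interview length: about 1.5 hours, or 90 minutes (Tool Development).
- Four districts and 35 enumerators (Field Coordination).

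**Assumptions (not in the article)**
- No true respondent effect.
- Four districts of equal size with scheduled-tribe shares of 2, 5, 12 and 25% (mean 44/4 = 11%, matching the stated total).
- District pace offsets of −0.5, −0.25, +0.25 and +0.5 times a spread of 5, 10 or 20 minutes.
- SD of interview time 20 minutes.

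**Formula.** With share s and pace offset p in each district, the artefact is Σ(s·p)/Σs − Σ((1−s)·p)/Σ(1−s).

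**Upper scenario: slowest district has the highest share, in perfect rank order, spread 5 minutes**
- Offsets: −2.5, −1.25, +1.25, +2.5.
- Scheduled tribe: (−0.05 − 0.0625 + 0.15 + 0.625)/0.44 = 0.6625/0.44 = 1.51.
- Others: (−2.45 − 1.1875 + 1.1 + 1.875)/3.56 = −0.6625/3.56 = −0.19.
- Difference: 1.69 minutes. It scales with the spread: 3.38 at 10 minutes and 6.77 at 20 minutes.

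**Naive standard error.** 20 × √(1/560 + 1/4535) = 0.90 minutes, so 1.96 SE = 1.76 minutes. The upper scenario is therefore 1.9, 3.8 and 7.6 standard errors from zero.

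**How far this depends on alignment.** Pairing the four paces with the four shares in all 24 possible orders gives:

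| Pace spread (min) | Smallest absolute artefact | Mean absolute artefact | Largest | Orders beyond 1.96 SE |
|---|---|---|---|---|
| 5 | 0 | 0.9 | 1.7 | 0 of 24 |
| 10 | 0 | 1.8 | 3.4 | 14 of 24 (58%) |
| 20 | 0 | 3.6 | 6.8 | 18 of 24 (75%) |

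The signed mean over the 24 orders is zero. Evenly spaced paces change the aligned values only slightly, to 1.6, 3.2 and 6.5.

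**Milder district differences.** With shares of 8, 10, 12 and 14%, the aligned artefact is 0.4, 0.9 and 1.8 minutes, or 0.5, 1.0 and 2.0 standard errors. If shares or paces do not differ between districts, it is zero.

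**Interruptions.** These shift a group comparison only if they differ by group. If the rate differed by 10 to 20 percentage points and each interruption lasted 10 to 20 minutes (both assumed), the shift would be 0.10 × 10 = 1 minute to 0.20 × 20 = 4 minutes.

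**The case against.** The best reply has four parts.

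1. *Table 1 is a one-line summary in a condensed article.* It says neither that the means are adjusted nor that they are not, and adjustment could sit in a fuller protocol or analysis plan. This stands against any claim that the plan fixes an unadjusted comparison. It does not remove the point that the definition given does not measure what its label says.

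2. *The enumerator side is already considered.* Profiles are collected and linked, and Table 2 uses both enumerator and respondent characteristics. This stands in part. Two enumerators with the same profile can still work at different speeds, and district is not named. The supervised models predict false or true labels, and k-means forms clusters; neither yields an adjusted group difference in time.

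3. *The premises behind any size are not documented.* Sociodemographic shares are given only overall, and no pace or variance is reported. This stands. A reader might take a null effect to look 2 to 8 standard errors from zero as a matter of course. That is the aligned extreme under assumed inputs, and it falls to zero when mix or pace is balanced.

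4. *Nothing follows automatically.* No threshold or action rule is attached to the indicator. The feedback section makes the response depend on magnitude and frequency and leaves the decision to the survey coordinator. The outcomes in Outcome Assessment do not use the indicator. This stands: a reader might infer that a group would be declared biased and handled differently, but the article does not tie such a step to this measure.

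Interruptions are disclosed as a limitation, and the article does not say that they differ by group. They cannot be presented as a demonstrated bias.

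**Conclusion.** The point holds in a limited form. As stated in Table 1, the indicator cannot attribute a difference in time to respondents, because the article's own account makes enumerators influential and assigns them by place. The profile linkage narrows the gap without closing it.

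The size cannot be determined from the article. Under the assumed shares, spreads and SD it lies between about zero and the aligned values in the table above. Once district pace differs by about 10 minutes in a 90-minute interview, perfect alignment is not needed for the artefact to pass 1.96 naive standard errors. At a 5-minute spread no ordering does so.

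No stated number is wrong. One monitoring indicator is affected, and the point is a worthwhile improvement rather than a threat to the study.

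**What to change.** Redefine the indicator as a within-enumerator contrast. Model log time with enumerator intercepts and district, and report the ratio of geometric mean times between sociodemographic groups with its interval. Table 1 could carry this in one line.

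Add a sensitivity analysis that leaves out interviews whose end-of-survey comments record an interruption. The main model needs this supplement: enumerator and district terms do not remove interruptions that differ by group, and the log scale only dampens them.

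If the simple mean is kept, label it as descriptive time by group rather than as respondent bias.

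The cost is analysis work, since times, respondent characteristics, comments and the enumerator linkage are already planned. The price in precision is wider intervals for groups rarely met by the same enumerator. If all 5095 women were interviewed and evenly spread, each enumerator would have about 5095/35 ≈ 146 interviews, of which about 0.11 × 146 ≈ 16 would be with scheduled-tribe women. Where mixing is uneven, some enumerators will add little to that contrast.

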During training, we spent time reviewing the paper versions of the tool as well as ensuring that our CAPI tablet versions, programmed using CSPro software, mirrored them well and adhered to the skip logic we had outlined. Both paper and tablet versions of the survey took on average about 1.5 hours to complete. The tablet version of the survey had just one question at a time appear on the screen. The process of checking the tablet version of the tool continued before and after piloting these versions in the field to ensure we had made all necessary changes in both language and logic before data collection with our end-line sample began. All survey data will be collected on tablets.

As part of the tablet-based data collection forms, we added a few parameters that were not part of the paper tools. These included time-stamps for the start and end of modules and time flags at the beginning and end of questions involving in-depth probing. GPS fields were added to the end of the tablet-based tool to track location.

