#### Field Monitoring

Field monitoring consists of both confirming the eligibility of respondents as well as spot checks. Both these aspects happen at each of the five levels of field hierarchy: (1) enumerator, (2) immediate field supervisor, (3) coordinator, (4) field-level data quality supervisor, and (5) back-end data quality supervisor. At the enumerator level, any issues or red flags identified by enumerators will be reported back to their immediate supervisor who assigned them to the interview; these could include issues of eligibility or issues with tablets or other interview processes. Immediate field supervisors will focus principally on locating respondents and monitoring interviews. The former occurs based on the respondents the field coordinators give each supervisor—the respondent is located, and eligibility is confirmed. Then the supervisor may monitor part or all of the interview either through spot-check observation or form check and keep track of completion or any needed follow-up visits. The coordinators will manage larger village/block level logistics to ensure all eligible participants in an area have at least been visited once on a trip and also complete random spot-checks as their logistics duties allow. The field level quality supervisor will complete spot-checks as well as follows-up on any systemic issues found in both eligibility checking or back-end data monitoring either by individually speaking with enumerators/supervisors or discussing any data quality issues during debriefing meetings with the team. Finally, the back-end data quality supervisor will check weekly data uploads for any entry errors relating to eligibility, such as incompatible birth age or incorrect unique identifier. They will also assess mechanistic indicators such as time to interview completion or rate of skips or “don’t know” responses that warrant further observation of participating enumerators. The larger research team will conduct monthly checks on the field teams.

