Beyond eligibility confirmations and observation spot-checks, our second stage of reliability monitoring will involve a 10% resample to ensure enumerators are asking the questions correctly so that we are getting consistent answers. A set of 15-25 questions will be randomly selected from a bank of 30, and the 10% sample will also be randomly selected from the total eligible population that has completed interviews. The recheck will be completed by a different enumerator either later in the day or a day later after the original interview has taken place.

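### Table 1's skip indicator does not separate skips required by the woman's answers from skips the enumerator causes, and the same required skips shorten the time indicator

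*Protocol article*

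**What the plan says.** Table 1 (under Building Models) gives the indicator for *Skipping of sections* as "Percent of skips across all potential skip options throughout the tool". The numerator is "Opportunities where a skip was implemented" and the denominator is "Total opportunities where a question or section can be skipped". Neither term distinguishes the reason for a skip.

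Tool Development says "All survey data will be collected on tablets" and that the CSPro version was checked so that it "adhered to the skip logic we had outlined".

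The rate is put to use. Field Monitoring has the back-end data quality supervisor look at "time to interview completion or rate of skips or" don't-know answers when deciding which enumerators need further observation. Building Models takes the step 1 features, which may include skip patterns, as model predictors.

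The *Rushed completion* row of Table 1 is pilot time minus actual time, divided by pilot time, for the survey, its sections and individual questions. It states no adjustment for how many questions were shown.

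The Discussion says that some skips and don't-know answers are "necessary and unavoidable; thus, these measures could be ambiguous at times". Data Analytics separately reviews item frequencies for unexpected skipping. Table 2 mentions respondent as well as enumerator characteristics in the intended application of each algorithm.

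**The concern.** When routing is programmed, a section can close because the woman's true answer closes it, or because the enumerator enters an untrue answer that closes it. Only the second is a quality failure, yet both enter the numerator equally. Two enumerators of equal quality will then have different skip rates if they interview different kinds of women, and a poor enumerator can look ordinary among women whose interviews are naturally long.

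The time indicator moves the same way. An honest interview with many required skips is short, so one cause in the woman's life shifts two features in the suspicious direction. A monitor or a model could take this as agreement between two pieces of evidence.

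At stake is who is picked for observation or retraining, and whether the outlier analysis finds poor interviewing or finds women with simple histories.

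**Working it through.** The document gives no skip rate, no number of gate questions and no spread between women, so there is no figure to reproduce. What follows is illustrative.

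**Inputs**
- From the article: 5095 women (Survey Description) and 35 enumerators (Field Coordination).
- Assumed: share of skip opportunities legitimately skipped, p = 0.2 to 0.6; share of the remainder improperly skipped, f = 0.05 to 0.20; between-woman SD of the skip rate, 0.10 to 0.20.

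**Step 1: what the indicator measures.** Raw indicator = p + (1 − p)f. Improper share of all counted skips = (1 − p)f / [p + (1 − p)f]. With f = 0.10:

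| p | raw indicator | improper share |
|---|---|---|
| 0.2 | 0.2 + 0.08 = 0.28 | 0.08/0.28 = 29% |
| 0.4 | 0.4 + 0.06 = 0.46 | 0.06/0.46 = 13% |
| 0.6 | 0.6 + 0.04 = 0.64 | 0.04/0.64 = 6% |

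Over the whole assumed range the share runs from 0.02/0.62 = 3% (p = 0.6, f = 0.05) to 0.16/0.36 = 44% (p = 0.2, f = 0.20). A raw value of 0.46 may mean p = 0.4 with 10% improper skipping, or p = 0.46 with none. The indicator cannot tell these apart.

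**Step 2: one interview against an enumerator's mean.** The shift at p = 0.4, f = 0.10 is 0.06. In one interview that is 0.06/0.20 = 0.3 SD to 0.06/0.10 = 0.6 SD. If all 5095 interviews were completed and shared equally, each enumerator would have 5095/35 = 145.6. The standard error of an enumerator's mean is SD/√145.6, that is 0.0083 to 0.0166, and the shift is 3.6 to 7.2 standard errors.

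That calculation requires women to be comparable across enumerators. If an honest enumerator's women legitimately skip 6 points more often, the same 3.6 to 7.2 standard errors appear with no misconduct. Averaging removes noise but not case-mix. The article gives reason to expect case-mix differences: work is assigned by location across four districts, and Study Setting and Population reports marked urban–rural differences in health behaviour.

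**Step 3: time.** Let an honest enumerator work at the pilot pace t per question, showing n questions where the pilot interview showed n₀. The whole-survey indicator is (t·n₀ − t·n)/(t·n₀) = 1 − n/n₀. It is positive whenever routing shows fewer questions than in the pilot, although nothing was rushed. Time per displayed question would be t in both, and the indicator zero.

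**Step 4: why a simple restriction is not enough.** Counting only questions due under the recorded routing would make the measure free of p, but a false gate answer makes the later questions look not due. The comparison has to be with what is expected for similar women.

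**The case against.** A reader might infer that the indicator reflects only the woman's circumstances and says nothing about enumerators. The document does not support that: routing follows the answers entered, so the rate rises when gates are falsely closed. A reader might also infer that the tablet makes discretionary skipping impossible. Tool Development says only that adherence to the skip logic was checked. Nor does a weak signal in a single interview show that the measure is useless, because Field Monitoring uses it to pick enumerators, whose means could show a consistent shift clearly if their women were comparable.

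The other side has further points:
- The authors disclose the ambiguity, and step 1 presents the features as provisional.
- The frequency review looks for unexpected skips, and Table 1 assigns fabricated answers to the 10% resample.
- Skips enter the models jointly with time and don't-know rates, and Table 2 names respondent characteristics. A predictor in a multivariable model need not be pure.
- Section and question times are compared as well as total time.
- Most consequences of a flag are mild.

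These points stand, but they cover the problem only partly. Disclosure does not change the definition. The frequency review does not alter the Table 1 feature. Building Models names the step 1 features as the predictors, and no expected skip rate is defined anywhere. Section and question times help with the time problem but leave the total unadjusted.

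**Conclusion.** The concern holds as a confounded definition. Table 1's skip indicator mixes required skips with improper ones, the total-time indicator inherits the same required skips, and the safeguards elsewhere in the article reduce this without removing it. It does not follow that the indicator carries no information on enumerators.

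The size of the effect cannot be obtained from the document. The 3% to 44% improper share and the 3.6 to 7.2 standard errors rest on assumed skip rates and spreads, independent interviews and equal workloads. They show that legitimate routing can make up most of the count, and that an enumerator-level signal is interpretable only after allowing for which women were interviewed.

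**What to change.** For enumerator monitoring and the outlier analysis:
1. Replace the raw percentage by observed minus expected skips (or gate-answer rates) per enumerator, with the expected value taken from women of similar characteristics in the same district.
2. Express time per question actually displayed, for survey and pilot interviews alike. Time-stamps were added only to the tablet forms, so the pilot value would come from tablet interviews.

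As a secondary check, make sure the main gate questions are in the recheck bank. The plan is: "A set of 15-25 questions will be randomly selected from a bank of 30". The bank's content is not shown, so some may be there already. Report, by enumerator, the gate answers that the recheck reverses towards not skipped. This cannot be a per-interview predictor, because only about 10% of interviews are rechecked. It is also thin for one enumerator: 0.10 × 145.6 = 14.6 rechecks, and if questions are drawn afresh each time, a given bank item appears in 15/30 = 50% to 25/30 = 83% of them, about 7 to 12.

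The cost is some extra analysis and some recheck slots, with no added fieldwork. One limit should be stated: the adjusted skip measure does not apply directly to the self-filled records labelled false, because they have no respondent from whom to predict an expected rate.
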